**1. The name of clinical study and design.**

Effects of chewing gum during pre-anesthetic fasting on preoperative anxiety and postoperative recovery in patients undergoing laparoscopic gynecological surgery with ERAS protocol: A randomized controlled study

**4. Study goals and background information**

1) Study goals

(1) Primary objective: This study aims to investigate whether sham feeding with sugar-free gum added to oral carbohydrates during pre-anesthetic fasting would relieve preoperative discomfort and anxiety in a patient undergoing laparoscopic gynecologic surgery.

(2) Secondary objective: Secondary objective is to investigate whether sham feeding with sugar-free gum added to oral carbohydrates during pre-anesthetic fasting would not only relieve preoperative discomfort and anxiety but also promote postoperative bowel function.

2) Rationale & background information

For patients undergoing surgery under general anesthesia, fasting for 6 hours of light meal and 2 hours of clear liquid is required in accordance with the ASA guideline to prevent complications such as gastric fluid regurgitation and pulmonary aspiration. Currently, the ERAS protocol has been introduced for enhanced recovery after surgery in patients undergoing various types of surgery, and it is recommended to allow clear liquids 2 hours before anesthesia and administer carbohydrate drinks during the fasting period. The administration of carbohydrates before surgery can prevent negative effects such as catabolic state and delayed recovery caused by fasting and improve patient satisfaction and well-being sense. The oral carbohydrate recommended to drink 400ml to 800ml up to 2 hours before surgery. The ERAS society suggests that chewing gum during the fasting period before surgery also has a positive effect and can be recommended. We previously studied the anxiolytic effect of chewing gum undergoing gynecologic surgery. (SMC 2019-05-168-001) Chewing gum during preoperative fasting is also thought to facilitate gastrointestinal movements, which will help restore gastrointestinal function. Previous studies have shown that sugar-free gum is not likely to affect the volume and acidity of the stomach immediately after anesthesia compared to patients who did not chew gum, and therefore the risk of regurgitation and pulmonary aspiration is not likely to make a big difference. However, the effect and safety profile of adding chewing gum to oral carbohydrates was not investigated.

We aim to investigate whether sham feeding with sugar-free gum added to oral carbohydrates during pre-anesthetic fasting would not only relieve preoperative discomfort and anxiety but also promote postoperative bowel function.

Currently, the Department of Obstetrics and Gynecology at our institution has decided to launch the ERAS protocol for patients scheduled to undergo elective laparoscopic gynecologic surgery. This study is a follow-up study on the anxiety-reducing effect of chewing gum during the fasting period before surgery. Patients participating in the ERAS protocol were set as a control group and sham feeding using gum was performed during the fasting period in the experimental group. The purpose of this study is to find out if chewing gum plus carbohydrate is effective in reducing anxiety and discomfort before surgery.

3) design: Single-center, randomized controlled study, investigator blinded.

**5. Study food**

1) Gum

(1) Name: Xylichew, Black Licorice (calories 5cal)

(2) Ingredient: Xylitol, gum base, vegetable glycerin, natural anise & licorice flavors, gum arabic, sunflower lecithin, carnauba wax. Xylitol, gum base, vegetable glycerin, natural anise & licorice flavors, gum arabic, sunflower lecithin, carnauba wax Xylitol, gum base, vegetable glycerin, natural anise & licorice flavors, gum arabic, sunflower lecithin, carnauba wax

2) Carbohydrate drink

(1) Name: NoNPO

(2) Ingredient: water, dextrin, sucrose, tomatine, sucralose, maltodextrin

**6. Study participants**

1) Inclusion criteria

(1) ASA class I-III adult patient (age 18 and under 70)

(2) Patients undergoing the laparoscopic gynecological surgery

2) Exclusion Criteria

(1) Pediatric (under 18)

(2) Old age (over 70)

(3) Pregnant and nursing mothers

(4) Patients with unstable vital signs (emergent conditions)

(5) Patients who are at high risk of aspiration: persons with a BMI of 30 or more, gastroesophageal reflux, achalasia, enteropathy, diabetes mellitus, and with a history of gastrointestinal tumor

(6) current medication affecting gastrointestinal motility

(7) uncontrolled liver or kidney disease

(8) Emergency surgery

(9) Patients who do not agree to participate in the study

3) Protection measures when recruiting vulnerable participants

All study subjects will obtain informed consent 1 day in advance and will spend at least 30 minutes sufficient time for explanations. In the case of subjects with reduced understanding and judgment, additional protective measures such as obtaining additional consent from the guardian (or representative) will be taken.

**7. Sample size calculation**

1) Primary hypothesis: The anxiety level of the group chewing gum while taking oral carbohydrate drinks during pre-anesthetic fasting will be lower than that of the group taking oral carbohydrate drinks.

2) Based on the results of the previous study, the mean of anxiety measured by VAS immediately before surgery when taking carbohydrate drinks was 34.83, and the standard deviation was 14.8. In addition, in the case of women, it was reported that the average value of anxiety before surgery was about 15% higher. Based on this, the VAS of preoperative anxiety in the female patient group immediately before surgery was corrected to 39.31 ± 17.04. Forty-seven patients in each group are needed to find the difference in the anxiety of 25% between the two groups, with 5% of alpha and power of 80%. Estimating a dropout rate of 10%, a total of 104 patients are needed, 52 in each group.

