**10. Outcomes and assessment**

1) Patient characteristics: Age, sex, height, weight, BMI, ASA class, and other comorbidities,

smoking, alcohol

2) Gastric fluid volume & pH

After taking the right lateral decubitus position, the diameter of the antrum is measured by abdominal ultrasonography.

The gastric fluid volume is calculated using the following formula.

* volume (ml) = 27 + 14.6 9 * antral area (cm²) – 1.289 * age (year)

After anesthesia induction is completed, gastric fluid is collected through an esophageal probe ad acidity is measured using a pH meter.

3) Pre-operative anxiety

(1) Anxiety with VAS

(2) Anxiety with APAIS score

[figure not shown]

The APAIS score was developed to measure patients' anxiety before surgery, and its effectiveness has been verified in several studies. The APAIS score is calculated by summing the scores from 1 to 5 for 6 questions. a

(3) Symptoms related to anxiety

Whether chewing gum during fasting helped to endure the fasting time, difficulty concentrating, and anxiety-related symptoms such as hunger, thirst, dry mouth, fatigue, headache, nausea, etc. were surveyed with a score between 0 and 10 for each item. do. (Questionnaire Attachment 1)

4) Recovery or bowel function

Post-operative nausea & vomiting

Flatus expulsion, defecation time in postoperative time, time of resume feeding

Intra-hospital bowel complication (ileus, dyspepsia, abdominal pain)

5) QoR15

QoR 15 is calculated by the total sum of the patient's postoperative recovery by asking questions on a scale from 0 to 10 for each item. The higher the score, the higher the quality of recovery.

6) Other Observation Items

(1) The amount of oral secretion at the time of intubation (none/ mild/ moderate/ severe)

(2) Total dose of the anesthetic drug used during anesthesia, amount of fluid

(3) Total anesthesia time and operation time

(4) Total amount of opioids used in the intrahospital period

7) Timeline

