**13. Outcomes and statistical analysis**

1) Primary outcome: Anxiety with APAIS score, Symptom related to anxiety

2) Secondary outcome: Flatus expulsion or defecation time in postoperative time, time of resume feeding, Intra hospital bowel complication, gastric fluid volume & pH, oral secretion at intubation time, QoR 15 score

3) Analysis

All continuous data are compared with Student’s t-test or Wilcoxon’s rank sum test according to normality. All categorical variables are analyzed using the chi-square test, Fisher’s exact test. The descriptive variables will be presented as mean ± standard deviation or median with an interquartile range. The categorical data are summarized as the number (%). The difference in APAIS, the primary outcome will be compared using student’s t-test. The multiple comparisons for sub-scores of APAIS would be adjusted with Bonferroni correction.

The association between QoR-15K and APAIS scores measured in the preoperative holding area will be analyzed using linear regression model.

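### The 80% power with 47 per arm is calculated for the anxiety VAS, but the primary outcome and primary test are on APAIS, so power for the primary analysis is undetermined

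*Protocol*

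**What the plan says.** Protocol section 7 builds the sample size on one instrument. Its source figure is that "the mean of anxiety measured by VAS immediately before surgery when taking carbohydrate drinks was 34.83, and the standard deviation was 14.8". After an adjustment for women, "the VAS of preoperative anxiety in the female patient group immediately before surgery was corrected to 39.31 ± 17.04". From these figures, "Forty-seven patients in each group are needed to find the difference in the anxiety of 25% between the two groups"; the calculation sets alpha at 5% and power at 80%. The total follows: "Estimating a dropout rate of 10%, a total of 104 patients are needed, 52 in each group". The primary hypothesis in the same section speaks only of the level of anxiety and names no scale.

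Protocol section 10 lists the VAS and APAIS as two separate measures of preoperative anxiety. On the second it says: "The APAIS score is calculated by summing the scores from 1 to 5 for 6 questions". The total therefore runs from 6 to 30.

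Protocol section 13 gives the outcome list: "Primary outcome: Anxiety with APAIS score, Symptom related to anxiety". The analysis text then treats APAIS alone as primary: "The difference in APAIS, the primary outcome will be compared using" Student's t-test. VAS anxiety appears in neither the primary nor the secondary list.

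**The concern.** Power is a property of a particular variable under a particular test. It depends on that variable's SD and on the difference to be detected. Section 7 supplies these for the VAS only, and section 13 tests APAIS. Nothing in the protocol carries the VAS assumptions over to APAIS, and no APAIS mean, SD or target difference is given.

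The 25% target does not carry over by itself. The APAIS total cannot fall below 6, so what a 25% drop means on it depends on a control mean that the protocol does not state.

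The main thing at stake is the sample-size justification: a reader of the APAIS result cannot rely on the stated 80%. The protocol also leaves two scales with a claim to be the main one, the VAS through the sample size and APAIS through the outcome list. Prespecification is meant to close off that choice. The symptom outcome listed beside APAIS as primary has no sample-size basis at all.

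**Working it through.** **Inputs from the protocol (section 7).** VAS control mean 39.31, SD 17.04, relative difference 25%, alpha 5%, power 80%, 47 per arm, 52 per arm after 10% dropout. Sidedness is not stated.

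**Step 1: reproduce the 47.**
- Target difference: 0.25 × 39.31 = 9.83 VAS points.
- Standardised difference: d = 9.8275 / 17.04 = 0.577.
- Normal approximation, two-sided 5%: n per arm = 2 × (1.960 + 0.842)² / d² = 15.70 / 0.3326 = 47.2, which is 48 when rounded up. Power at 47 is 79.8%.
- Two-sample t-test: 48.2 per arm; power at 47 is 79.0%.
- A one-sided 5% test would need only 38 per arm, so the stated figure matches a two-sided test.

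The 47 is thus reproduced to within about one patient, and it comes from a VAS comparison.

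**Step 2: what 47 per arm delivers on any outcome.** The difference detectable with 80% power is d = (1.960 + 0.842) × √(2/47) = 0.578 SD by normal approximation, or 0.584 SD by the t-test. In APAIS points this depends on the SD, which has to be assumed:

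| Assumed APAIS SD | Difference with 80% power (0.584 × SD) |
|---|---|
| 3 | 1.75 |
| 4 | 2.34 |
| 5 | 2.92 |
| 6 | 3.50 |

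**Step 3: power on APAIS if the 25% target were applied to it.** The control means and SDs below are assumptions, not figures from the protocol. Entries are power at 47 per arm, two-sided 5%, normal approximation.

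| Assumed control mean (25% drop) | SD 3 | SD 4 | SD 5 | SD 6 |
|---|---|---|---|---|
| 10 (2.5 points) | 98.1% | 85.8% | 67.9% | 52.4% |
| 12 (3.0 points) | 99.8% | 95.3% | 82.9% | 67.9% |
| 14 (3.5 points) | >99% | 98.9% | 92.4% | 80.7% |
| 16 (4.0 points) | >99% | 99.8% | 97.2% | 89.8% |

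The corresponding need runs from 9 per arm (mean 16, SD 3) to 91 per arm (mean 10, SD 6). The stated 80% could therefore be too high or too low for APAIS, and the protocol gives no way to tell which.

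**Step 4: how far a 25% drop moves the APAIS total.** Only the part above the floor of 6 can move. At an assumed mean of 15 the drop is 0.25 × 15 = 3.75 points out of 15 − 6 = 9, or 42%. At a mean of 10 it is 2.5 out of 4, or 62.5%. Whether a 25% drop is a realistic target on this scale needs its own justification.

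**The case against.** **Both scales measure the same thing.** The hypothesis is about anxiety, section 10 places the two scales side by side, and a VAS result would bear on that hypothesis. This stands: a VAS finding would be relevant, though the VAS is not a listed outcome. It does not rescue the power statement, because a shared construct fixes neither the SD nor the target difference of the variable tested.

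**A null APAIS result could still be read from its confidence interval.** This also stands. What is lost is the claim of 80% power, not the interpretability of the trial.

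**A statistical analysis plan might settle it.** The point does not turn on a missing detail. Two sections of the protocol rest on different outcomes, and the protocol itself has to agree on its primary outcome and on the basis for its size.

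**The stronger reading.** A reader might infer that the trial is underpowered. With an assumed true difference of 2 APAIS points, for example, power at 47 per arm would be 67%, 48% or 36% for an SD of 4, 5 or 6. But 2 points is not the protocol's target and appears nowhere in it. With the protocol's own 25% and an assumed mean of 15 (3.75 points), the same SDs give about 99%, 95% and 85%. The documents support neither set over the other.

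**Conclusion.** The point holds as a mismatch. The stated 80% is reproduced for a VAS comparison (79% to 80% at 47 per arm), while the declared primary test is on APAIS, for which the protocol gives no planning values. Power on APAIS is undetermined. It is 80% only if the true difference is about 0.58 SD, and it ranges from about 52% to over 99% under the assumed means of 10 to 16, SDs of 3 to 6 and a 25% drop. The mismatch itself rests on the protocol's text alone; the range rests on those assumptions and on a two-sided 5% test.

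The documents do not show that the trial is too small, or that the VAS would be the better primary outcome. Section 10 claims validation in earlier work for APAIS only, and the choice of scale is the sponsor's. The same gap applies to the anxiety-related symptoms, which section 13 lists as primary without any sample-size basis.

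**What to change.** Keep 104 patients and make sections 7 and 13 use the same single primary outcome.

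- **If the APAIS total stays primary:** replace the VAS-based 80% in section 7 with what 47 per arm delivers on APAIS, namely 80% power for about 0.58 SD at two-sided 5%. Convert this to points with an SD from a cited source, and say whether a difference of that size is worth detecting. List VAS anxiety as a secondary outcome in section 13.
- **If the sponsor prefers the VAS on which the trial was sized:** name VAS anxiety in the holding area as the single primary outcome in section 13, amend the analysis text to test it, and make the APAIS total a key secondary outcome.

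In either case, move the anxiety-related symptoms to secondary.

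The cost is a short amendment to the outcome list and either the power statement or the analysis text. Both scales are already collected, so no new measurement is needed. If APAIS is kept, the stated power may turn out less favourable than 80%.

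### Section 7's corrected control mean of 39.31 is not 15% above 34.83, and on the printed inputs 47 per group gives about 79% power rather than 80%

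*Protocol*

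**What the plan says.** All the figures stand in one paragraph of the protocol, section 7 (Sample size calculation).

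- Source values: "the mean of anxiety measured by VAS immediately before surgery when taking carbohydrate drinks was 34.83", and "the standard deviation was 14.8".
- Adjustment for a female population: "the average value of anxiety before surgery was about 15% higher". On that basis, "the VAS of preoperative anxiety in the female patient group immediately before surgery was corrected to 39.31 ± 17.04".
- Target: 47 per group "to find the difference in the anxiety of 25% between the two groups", at 5% alpha and 80% power. Neither the sidedness nor the formula is given.
- Inflation: "Estimating a dropout rate of 10%, a total of 104 patients are needed, 52 in each group".

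Section 13 (Outcomes and statistical analysis) names Student's t-test for the primary comparison.

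**The concern.** The adjusted mean is presented as the source mean raised by about 15%, but the two printed means do not stand in that ratio, while the two SDs do. One correction appears to have been applied at two rates, so at least one printed mean is wrong.

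The adjusted mean also fixes the target effect, because the detectable difference is a percentage of it. A change in the mean changes the difference in points, the standardised effect and the number per group. This paragraph is the only justification for 104 patients. As printed, a reader cannot reproduce it or tell which inputs gave 47.

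**Working it through.** **Inputs** (section 7 unless noted): source mean 34.83, SD 14.8; increase of 15%; printed control values 39.31 ± 17.04; relative difference 25%; alpha 5%; power 80%; 47 per group; 10% dropout; 52 per group. The test is the t-test (section 13). *Assumption:* two-sided, since sidedness is not stated.

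**1. The adjustment**

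- Mean: 34.83 × 1.15 = 40.05. Printed: 39.31. Ratio 39.31/34.83 = 1.129, or +12.9%.
- SD: 14.8 × 1.15 = 17.02. Printed: 17.04. Ratio 17.04/14.8 = 1.151, or +15.1%. The gap of 0.02 is rounding: 17.04/1.15 = 14.82, which prints as 14.8.
- The mean has no such explanation. Working back, 39.31/1.15 = 34.18, which does not round to 34.83.

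**2. Number per group**

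Normal approximation: n = 2 × [(1.960 + 0.842) × SD / Δ]². The t-test figures use the noncentral t distribution.

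| Inputs | Δ = 25% of mean | Δ/SD | n, normal | n, t-test | Power at 47, normal | Power at 47, t-test |
|---|---|---|---|---|---|---|
| 39.31 ± 17.04 (printed) | 9.83 | 0.577 | 47.2, so 48 | 48.2, so 49 | 79.8% | 79.0% |
| 40.05 ± 17.02 (true 15%) | 10.01 | 0.588 | 45.3, so 46 | 46.3, so 47 | 81.4% | 80.6% |

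The plan's 47 is reproduced exactly by the t-test on 40.05 ± 17.02. The unadjusted 34.83 ± 14.8 has the same ratio of mean to SD and also gives 47. On the printed inputs, 47 appears only if the normal-approximation result of 47.2 is rounded down. A one-sided test on the printed inputs gives 38, so it does not explain 47.

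**3. Dropout**

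- Dividing by the retained fraction: 47/0.9 = 52.2, so 53 per group (106).
- Multiplying instead: 47 × 1.1 = 51.7, so 52. This matches the plan.
- Expected evaluable number from 52: 52 × 0.9 = 46.8 per group, which is 0.2 of a patient below 47.

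**4. Power of 104 randomised after 10% loss** (46.8 per group, two-sided t-test)

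- 39.31 ± 17.04: 78.8%.
- 40.05 ± 17.02: 80.4%.

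**The case against.** The strongest reply is that nearly all of this is rounding. The documents say *about* 15%. Section 7 names no formula, and under the normal approximation 47 per group gives 79.8%, which anyone would report as 80%. Section 13 names the t-test for the APAIS score, whereas section 7 sizes on VAS, so the exact t calculation is not strictly the one the plan promised. Multiplying by 1.1 is a common shortcut that costs one patient per group. The inputs are soft in any case, and a one-point difference in power has no consequence for design or ethics.

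Most of that stands as a statement about size. It does not rescue the mean. The word *about* cannot cover 12.9% when the SD in the same sentence moves by 15.1%, and a figure that does not follow from its stated basis is an error whatever its effect.

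A reader might go further in three ways that the documents do not support:

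- *The slips compound.* They do not all act in one direction. If 40.05 is right, printing 39.31 understates the target difference (9.83 against 10.01 points) and so calls for more patients, which is conservative.
- *A 10% loss leaves 46 per group.* Losing 6 of 52 is 11.5%. Ten per cent of 104 is 10.4, which leaves 93.6, or 46.8 per group. Losing 10 patients in all leaves 94, an average of 47 per group.
- *The source mean has transposed digits.* The value that would yield 39.31 is 34.18, and this is not a transposition of 34.83. Swapping the last two digits gives 34.38, and 34.38 × 1.15 = 39.54. The documents do not show which of the two means is misprinted.

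**Conclusion.** The point holds as an internal contradiction with a small effect. The corrected mean of 39.31 does not follow from 34.83 and 15%. With the inputs as printed, 47 per group falls just short of the stated power (79.8% by normal approximation, 79.0% by t-test). The dropout step falls short by 0.2 of an expected patient, or one patient per group after rounding up.

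These figures do not show that the trial is too small. If the mean should read 40.05, then 47 per group is right, and 104 randomised patients still deliver about 80% after 10% loss. If 39.31 stands, they deliver about 79%. The most at stake is therefore about one point of power.

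This rests on a two-sided 5% test, an exact 15% increase, equal SDs in the two groups and a 10% loss spread evenly between them. That 40.05 is the intended mean is plausible, because it reproduces 47 exactly, but it remains an inference.

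**What to change.** In section 7:

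1. Check the mean against the source study and correct whichever of 34.83 or 39.31 is misprinted, so that the mean and SD carry the same 15% increase.
2. State the sidedness and the formula used.
3. Restate the power that 104 randomised patients give after 10% loss (about 46.8 per group, t-test): about 79% if 39.31 ± 17.04 stands, about 80% if the mean is 40.05 ± 17.02. If the dropout allowance is recalculated, show it as division by 0.9.

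The cost is one corrected paragraph and, if 39.31 is kept, a stated power about one point lower. No change in enrolment is needed.

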**8. Study period**

1 year from the clinical trial approval date

**9. Methodology**

1) Time flow

1. The patient is assigned to either the experimental group or control group on a random basis on the eve of the operation. All patients scheduled for gynecologic surgery were instructed to fast overnight before surgery, and oral carbohydrate drink (NO NPO^Ⓡ^: Daesang, Seoul, South Korea) loading was used routinely according to the protocol of the department of gynecology
2. The patients in the control group (CHD group) are requested to follow the aforementioned fasting guideline. The participants were instructed to consume at least 600 mL to 800 mL of carbohydrate drinks up to 3 hours before induction of anesthesia.
3. The patients in the test group (CHD with gum group) follows the fasting protocols of our gynecologic strategy and were encouraged to chew gum freely with oral carbohydrate loading during fasting time.
4. There is no intervention other than chewing gum during fast times between the two groups of patients.
5. Gum will be removed right before being transported to the operating room before transfer. The nurse in charge of the operating room double-checks whether or not gum has been removed during the patient identification process in the preoperative holding area.
6. The severity of anxiety would be examined at the preoperative holding area immediately before surgery.
7. In the operating theater, all participants are provided with supplemental oxygen. During pre-oxygenation, a gastric ultrasound exam is performed by [name].
8. The independent anesthesiologist will induce general anesthesia according to the standardized protocol. Propofol and remifentanil are used using a TCI machine with the aim of a Bispectral Index of 40-60. Blood pressure and heart rate were maintained within 10% of baseline. The blinded anesthesiologist will rate the oral secretion during tracheal intubation.
9. Gastric juice is naturally drained via an esophageal temperature probe (ST probe) during surgery and analyzed with an acidity analyzer.
10. In the course of surgery and maintenance of anesthesia, the subsequent process proceeds without special intervention. Total anesthesia time, operation time, drugs used during anesthesia, and vital signs are collected through medical records. (Attachment of case reporting form)
11. Afterward, the treatment and recovery of patients in the ward will be proceeded according to the general guidelines of the department of obstetrics and gynecology based on the ERAS protocol.

- **standardized anesthesia protocol**

Standard ASA monitoring including noninvasive blood pressure, EKG, pulse oximetry, and bispectral index (BIS) monitoring will be applied. After denitrogenation with 80 % oxygen, general anesthesia will be induced with propofol and remifentanil using target-controlled infusion (Orchestra® Base Primea; Fresenius Kabi, Brezins, France), and intravenous rocuronium 0.8 mgkg^-1^. Another investigator who is not aware of group allocation will perform intubations and evaluate the degree of oral secretion during intubation. After tracheal intubation via video stylet, the ventilator was set with a tidal volume of 8 mLkg^-1^of ideal body weight and FiO_2_ 40 %. The respiratory rate and I: E ratio were adjusted to maintain inspiratory peak pressure of less than 30 cmH_2_O and normocapnia. During the whole surgery, propofol and remifentanil effect site concentrations will be adjusted to achieve BIS values of 40 to 50 and to maintain mean blood pressure and heart rate within 20 % of pre-induction values.

- **Postoperative management protocol**

Postoperative analgesia is standardized for all patients. If patients presented with breakthrough pain (NRS ≥ 4/10), IV ibuprofen 400 mg will be administered. If this proved ineffective after 30 minutes IV pethidine 50 mg will be administered. Postoperative nausea and vomiting are treated with intravenous metoclopramide 10 mg and ramosetron 0.3 mg. All patients resume diet and ambulation as soon as possible after full recovery from anesthesia unless gastrointestinal symptoms are noted. Hospital discharge is determined by the surgery team.

2) Randomization and blinding

The patient is assigned to either the experimental group or control group on a random basis on the eve of the operation. There is no intervention other than chewing gum during fast times between the two groups of patients, and subsequent anesthesia and pre-anesthesia examinations will be conducted according to a standardized protocol. The randomization list was generated by a random permuted block design with a block size of two. The allocation information is sealed in an opaque envelope and piled up in a cabinet. Gynecologist open the sealed envelope, in turn, to confirm the assignment information and distributed or not distributed chewing gum, accordingly. Randomization information is managed so that the list is not disclosed to the evaluator and only primary investigators can know. After entering the operating room, both the control group and the test group proceed according to the same study protocol, and both gastric volume measurements and acidity records are recorded by the [name]. Anxiety levels prior to surgery and uncomfortable symptoms related to fasting will be recorded by an anesthesiologist who is not participating in the study based on patient self-report. Postoperative gastrointestinal motility recovery and postoperative recovery questionnaires were completed by the patient under the guidance of an independent maternity ward nurse and attending physician.

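### Scheduled operating slot and planned operation are left out of the listed baseline data and the fixed analyses; prespecifying them as covariates would be a cheap gain in precision, not the repair of a bias.

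*Protocol*

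**What the plan says.** - **Fasting and exposure.** Protocol section 9, Time flow, item 1: "All patients scheduled for gynecologic surgery were instructed to fast overnight before surgery". Item 2 allows the carbohydrate drink until 3 hours before induction. Under item 3, gum patients are "encouraged to chew gum freely with oral carbohydrate loading during fasting time"; no amount or duration of chewing is set. Item 5 has the gum removed just before transfer to the operating room.
- **Eligibility.** Section 6 admits "Patients undergoing the laparoscopic gynecological surgery", with no restriction on extent or indication.
- **Allocation.** Patients are allocated on the eve of surgery. "The randomization list was generated by a random permuted block design with a block size of two"; no stratification factor is named.
- **Listed baseline data.** Section 10, item 1: "Patient characteristics: Age, sex, height, weight, BMI, ASA class, and other comorbidities", followed by smoking and alcohol. Scheduled slot, fasting length and planned operation are not listed. Total anesthesia and operation time are listed among the other observations.
- **Analysis.** Section 13: "The difference in APAIS, the primary outcome will be compared using" Student's t-test. Other continuous data get a t-test or rank-sum test. The only regression relates QoR-15K to APAIS and is not a comparison of arms.

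**The concern.** The fast starts overnight for everyone and stops at surgery. A patient early on the list has a shorter fast and less waking time in which to chew than a patient later in the day. Slot therefore plausibly affects the amount of intervention received, the fasting symptoms (hunger, thirst, dry mouth, fatigue) that section 13 places in the primary outcome, and perhaps anxiety itself. Extent of operation plausibly affects the bowel-recovery outcomes and QoR-15.

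Both factors precede allocation if taken as scheduled and planned. If they predict outcome and are left out of the model, their variance stays in the error term, and a chance difference between arms in either is carried into the estimate. Operation time does not fill the gap, because it is known only after allocation. What is at stake is the width of the confidence interval and the credibility of the estimate given the imbalance that actually occurs.

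**Working it through.** **Inputs from Protocol section 7.** Control mean and SD on the anxiety VAS: "immediately before surgery was corrected to 39.31 ± 17.04". Target difference 25%. Error rates: "with 5% of alpha and power of 80"%. 47 per arm, 52 after dropout. Sidedness is not stated; two-sided is taken.

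**Step 1: reproduce the plan's figure.**
- Difference = 0.25 × 39.31 = 9.83 mm; standardised, 9.83 / 17.04 = 0.577.
- Normal approximation: n = 2 × (1.960 + 0.842)² / 0.577² ≈ 47.2, so 48 when rounded up, against the stated 47. The exact t calculation needs 49.
- Power at 47 per arm is 79.8% (normal) or 79.0% (exact t). The stated size reproduces to within two patients. Exact t is used below.

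**Step 2: gain from adjustment.** For a binary factor held by a proportion p that shifts the outcome by s, R² = p(1 − p)s² / SD². Adjustment replaces the SD by SD × √(1 − R²) and costs one degree of freedom. Assumed, because the documents give neither: p = 0.4 first cases, s = 5 to 14 mm.

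| Assumed slot shift | R² | Residual SD | Power at 47 per arm |
|---|---|---|---|
| none (unadjusted) | 0 | 17.04 | 79.0% |
| 5 mm | 2.1% | 16.86 | 79.8% |
| 8 mm | 5.3% | 16.58 | 81.1% |
| 12 mm | 11.9% | 15.99 | 83.8% |
| 14 mm | 16.2% | 15.60 | 85.6% |

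As a scale for these shifts, 5 mm is about half the planned gum effect (5 / 9.83 = 51%), and 8–14 mm is 81–142% of it.

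**Step 3: chance imbalance.** Treat the number of first cases in each arm as an independent Binomial(52, 0.4). The arms then differ by at least 10 percentage points in 27.1% of trials and by at least 15 points in 13.3%. A 15-point imbalance moves the unadjusted difference by 0.15 × 8 = 1.2 mm to 0.15 × 14 = 2.1 mm. The standard error at 52 per arm is 17.04 × √(2/52) = 3.34 mm, so this is about 0.4 to 0.6 of a standard error.

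**Step 4: what cannot be computed.** Section 7 plans on the VAS, while section 13 tests APAIS and gives no SD for it. The protocol also gives no SD or target effect for flatus, defecation or QoR-15. No power gain is claimed for any of these.

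**The case against.** **The unadjusted test is not an error.** This stands. Randomization makes it valid, and its 5% error rate already allows for chance imbalance. A reader might infer that leaving out slot biases the comparison; nothing in the protocol supports that.

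**The gain is assumed.** This stands too. No slot effect is documented, and a shift of 8–14 mm makes slot about as important as the treatment. At 5 mm the gain is under one percentage point. The imbalance effect lies well within ordinary sampling error.

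**The data may be collected anyway.** The case report form is a separate attachment, and the operating schedule and chart would hold both items. It would therefore go too far to say that imbalance could not be seen or corrected. The documents show only that the protocol's lists omit these factors and that its stated analysis does not use them.

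**The mechanism is partly inferred.** No section says that the slot is fixed at allocation. It is a fair inference, since patients are scheduled and must time their drink to induction. That same drink rule ties the clear-fluid fast to induction, so slot mainly changes the solid-food fast and the chewing window.

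**A null result diluted by little chewing.** One might argue that, without slot, a null result could merely reflect gum patients with hardly any waking fast. A model with arm and slot would not cure that: it removes noise but neither measures nor restores exposure. The recommendation does not rest on this argument.

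**It belongs in a SAP.** Adjustment could be specified there, but section 13 already commits the primary comparison to a t-test. That stated choice can be improved.

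**Conclusion.** The point holds as a low-cost improvement to a stated analysis. The protocol ties the chewing window to an overnight fast that ends at surgery and admits any laparoscopic gynecological operation, yet its listed data, allocation and tests take account of neither slot nor planned operation. The consequence is lost precision and less protection against conditional imbalance; the type I error rate is unaffected.

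On the VAS planning scale at 47 per arm, the gain runs from under 1 power point (R² about 2%) to between 2 and 7 points (R² about 5–16%). It rests on an assumed 40% of first cases and assumed slot shifts. Its size for APAIS, the symptom scores and the bowel outcomes is unknown. Because the stated size gives 79.0% by exact t, just under its own target, even a modest gain is worth having at this price.

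**What to change.** 1. Before the envelope is opened, record from the operating schedule the scheduled slot (first case or later) and the planned operation class.
2. In section 10, add both to the patient characteristics.
3. In section 13, replace the t-test for APAIS and the symptom scores with a linear model containing arm and scheduled slot. Prespecify slot and planned operation class as covariates for flatus, defecation and QoR-15. Use the scheduled and planned values, whatever happens on the day.
4. Report actual fasting duration and the arm difference by slot descriptively only. Actual duration is known only after allocation and should not be a covariate.

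The cost is one to three degrees of freedom, a few case-report-form fields and a paragraph of analysis text. Separate envelope stacks by slot are not needed. The wording should be settled before outcome data are seen.
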